### Eligibility criteria

Approximately 50 volunteers will be recruited from respiratory patients undergoing lung surgery with general anesthesia lasting 2–8 hours. As previously mentioned, this is a pilot study, so 25 volunteers in each group should be enough to provide information on the changes in cognitive function. Participants must be native Japanese speakers who are 60 years and older and self-report to be right-handed. Participants should be unconcerned with their memory functions. A thoracic surgery physician from the Tohoku University Hospital will refer potential participants. Other data that will be recorded includes the type of general anesthesia, the amount of anesthesia administered, duration of anesthetic administration, duration of surgery, age, and sex. These additional data will be collected by the collaborating surgeons.

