### Sample size

This is a pilot study. Because a similar study has not been conducted, calculation of a sample size is not possible. However, we will aim to include 50 participants.

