### Statistical analysis

This study is designed to 1) determine whether there is a decline in cognition after lung surgery in elderly patients and 2) evaluate the beneficial effect of SCRA cognitive intervention in this patient population. The analysis will be based on the intention-to-treat principle.

For comparison of cognitive function before and after surgery, a Wilcoxon Signed-Rank test will be used to compare all participants in both groups. This will determine whether cognitive functions declined postsurgery. Participants will have been randomly placed into a group receiving SCRA intervention, or a waitlisted control group. To evaluate the effects of the cognitive intervention, we will calculate the change in score (post-training score minus pre-training score) for each measure and conduct a between-group variance ANCOVA test. The change in scores is the dependent variable, while the treatment group (cognitive intervention group, waitlisted control group) is the independent variable. Pretraining scores in the dependent variable, sex, and age categories are the covariates to exclude the possibility that any pre-existing difference of measure between groups will affect the result of each measure and to adjust for background characteristics. This is a pilot study that will likely be conducted with a small number of participants, and the effects are unlikely to be significant.

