The level of significance is set at *p* < 0.05. However, since this study includes six different cognitive tests (MMSE-J, FAB, and four computerized tests), we will use Benjamini and Hochverg’s false discovery rate (FDR) correction methods to adjust the *p* values [65]. As a result, the statistical threshold of the behavioral data was set at *p* < 0.05, FDR-corrected. Moreover, we will report eta squared (h2) as an index of the effect size. This index is the standardized difference in the change score between the intervention groups (cognitive intervention group, waitlisted control group). In actuality, h2 ≥ 0.01 is regarded as a small effect, h2 ≥ .006 as a medium effect, and h2 ≥ 0.14 as a large effect [66]. The level of significance is set at *p* < 0.05. Missing data are imputed using the multiple imputation method, as implemented in the Statistical Package for the Social Sciences (SPSS). SPSS uses a fully conditional specification, or chained equations, imputation algorithm. Essentially, incomplete variables are individually imputed and uses the filled-in variable as a predictor in all subsequent steps. Linear regression is used for continuous variables, and logistic regression is used for categorical variables [67]. All randomized participants are included in the analyses in line with their allocation, irrespective of how many sessions they complete (intention-to-treat principle). All statistical analysis will be conducted using SPSS software (Statistical Package for Social Science).

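### The medium cut-off for eta squared (.006) lies below the small one (0.01), and the index is misdescribed as a standardized difference; descriptive labels are affected, not the tests

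*Protocol article*

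**What the plan says.** The relevant text is in the protocol article, Statistical analysis. The intervention is assessed by an ANCOVA of the change score on each cognitive measure, with the pre-training score, sex and age as covariates. Significance is judged at 0.05 after false discovery rate correction over six cognitive tests.

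On effect size the section says "we will report eta squared (h2) as an index of the effect size" and then explains: "This index is the standardized difference in the change score between the intervention groups". The grading follows, with a literature citation: "h2 ≥ 0.01 is regarded as a small effect", "h2 ≥ .006 as a medium effect" and "h2 ≥ 0.14 as a large effect". No other part of the article corrects the cut-off or the definition.

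On size, the Sample size section says "we will aim to include 50 participants", and Eligibility criteria puts 25 in each group. The analysis section expects that "the effects are unlikely to be significant".

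**The concern.** There are two separate errors.

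**Order of the cut-offs.** An ascending scale needs 0.01 < medium < 0.14. With medium at .006, any value that qualifies as small has already qualified as medium, so no result can be graded small only.

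**Definition of the index.** Eta squared is a share of variance: it lies between 0 and 1 and has no sign. A standardized difference is signed and on another scale. The plan names one statistic and describes another. The missing sign matters here because lower scores are better on two of the six tests (the Cogstate detection and identification tasks) and higher scores are better on the other four. The index alone does not show which group did better.

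At stake is how the results are described. With non-significant p values expected and no sample-size calculation, readers are likely to look at the effect sizes, including when a later trial is planned. A medium label that chance alone often produces would mislead them.

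**Working it through.** **Inputs.** From the article: N = 50, allocation 1:1 (25 per group), three covariates, six cognitive tests, cut-offs 0.01 / .006 / 0.14. Assumed: one degree of freedom per covariate, giving error df = 50 − 2 − 3 = 45; no true effect; labels applied as printed, with the higher of two satisfied labels used. The article does not say whether eta squared is partial or classical, so both are shown.

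**1. Do the printed cut-offs fit together?** For two equal groups, η² = d²/(d² + 4). Taking d = 0.2, 0.5 and 0.8 as small, medium and large (an assumption):

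- d = 0.2: 0.04/4.04 = 0.0099
- d = 0.5: 0.25/4.25 = 0.059
- d = 0.8: 0.64/4.64 = 0.138

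The printed 0.01 and 0.14 are reproduced. The printed .006 is not: it corresponds to d = 2√(.006/.994) = 0.155, less than the small benchmark. A medium value of 0.06 fits, so a misplaced decimal is the likely cause.

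**2. Partial eta squared under no effect.** For a 1-df group effect, η² = F/(F + 45), which follows a Beta(1/2, 45/2) distribution. Inverting, F = 45η²/(1 − η²).

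| Cut-off | F needed | Chance of reaching it |
|---|---|---|
| .006 (printed medium) | 0.27 | 60.5% |
| 0.01 (small) | 0.45 | 50.4% |
| 0.06 (medium if corrected) | 2.87 | 9.7% |
| 0.14 (large) | 7.33 | 1.0% |

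The median under no effect is 0.010 and the mean is 1/46 = 0.022; both exceed .006. The chance of landing in the medium band (below 0.14) is 60.5 − 1.0 = 59.5% as printed and 9.7 − 1.0 = 8.7% with 0.06.

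**3. Expected number of the six tests at medium or above.** As printed, 6 × 0.605 = 3.6. With 0.06, 6 × 0.097 = 0.58. An expected count does not require the tests to be independent.

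**4. Sensitivity to N and covariates.** For N from 30 to 60 and 0 to 5 covariate df, the chance that partial eta squared reaches .006 runs from 56% to 71%.

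**5. Classical eta squared (group sum of squares over total).** This was simulated at N = 50 with 20,000 trials per setting and no group effect. The share of variance explained by the covariates is not given in the article, so it is varied.

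| Variance explained by covariates | Chance of reaching .006 | Chance of reaching 0.06 |
|---|---|---|
| 0% | 59% | 8.7% |
| 30% | 52% | 4.3% |
| 40% | 49% | 2.7% |
| 50% | 44% | 1.6% |
| 60% | 40% | 0.8% |

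**The case against.** The strongest reply is that nothing is decided by these cut-offs. Inference rests on FDR-adjusted p values, and the eta-squared scale is a cited convention added for description. That stands, and it limits the point to labelling.

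A reader might go further and infer that chance differences will usually be reported as medium benefits and that these labels will carry the trial's conclusion. The documents do not support that. The article speaks of effects, not benefit, and nowhere says the labels will decide the interpretation. Its Discussion responds to the expected lack of significance by calling for a larger repeat study. *Usually* is also too strong, since for classical eta squared with strong covariates the chance falls to 40–49%.

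A reader might likewise infer that at least one medium label is almost certain: 1 − (1 − 0.605)⁶ = 99.6%. That treats as independent six tests taken by the same patients, which the article does not support. The same sum with 0.06 already gives 46%.

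Three further replies have some weight:

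- If medium were read as only .006 to 0.01, about 10% of chance results would fall there. That reading would put medium below small, so it does not rescue the scale.
- About half of chance results (50.4%) reach the small cut-off even on a corrected scale. That reflects N = 50, not the misprint. What the misprint adds is the wrong label.
- The direction of effect can be recovered from group means, and the article states which direction is better on each cognitive test. The lack of sign is therefore a limit of the index, not proof that the report will hide direction.

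That the cut-off is plainly a slip does not remove it from a prespecified scale, and a decimal slip does not explain the wrong definition.

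**Conclusion.** Both errors are present as written: the medium cut-off is below the small one, and eta squared is described as something it is not. Taken literally with no true effect at N = 50, roughly 40–60% of results per test would reach medium, against about 10% for partial eta squared with 0.06.

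The upper figure rests on partial eta squared with 45 error df. The lower rests on classical eta squared with covariates explaining 60% of the variance. All of them assume the scale is applied as printed. The FDR-adjusted p values, the type I error and the sample size are unaffected. This is an error in descriptive effect-size labels, and it has some weight because the plan itself expects non-significant results.

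**What to change.** 1. Change the medium cut-off from .006 to 0.06.
2. Replace the definition: eta squared is the proportion of change-score variance attributed to treatment group. State whether the partial or the classical form is used.
3. Beside eta squared, report for each test the adjusted between-group mean difference with its 95% CI, so that direction and precision are visible. This is a recommendation that follows from the unsigned index; an article need not spell out every reporting detail.

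The cost is one number, one sentence, and output that the planned ANCOVA already produces. No change to design, sample size or testing is needed. It should be done before any result is labelled.

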### Data monitoring and auditing

We will follow the recommended guidelines for clinical research in Japan (http://www.mhlw.go.jp/topics/bukyoku/seisaku/kojin/dl/161228rinsyou.pdf). According to the guidelines, data monitoring by a third party is unnecessary for this study since we are not providing participants with any medications, nor are we conducting surgery.

### Risks and benefits to participants

Participants are unlikely to encounter any serious risks or burdens. Nevertheless, the three cognitive tests together are expected to take 1 hour. Therefore, participants will possibly experience fatigue and discomfort during testing. The participant will be informed in advance that, should they feel any discomfort, the test can be interrupted at any time. In addition, this study requires participants to undergo cognitive training for 12 weeks. The training tasks (reading aloud and solving simple arithmetic) are not particularly difficult and should not cause the participants any pain. However, if for some reason the participant experiences pain, they will have been previously informed that they may immediately interrupt the training.

In accordance with the provisions of the university, the participants will be given a monetary reward. The reward amount is based on the number of hours invested. Therefore, should the participant decide to leave partway through the study, the reward amount received will coincide with the number of hours they partook.

### Ethics and dissemination

The protocol of the study and the consent form were approved by the Ethics Committee of Tohoku University Graduate School of Medicine. Participants will be given both an oral explanation and a written file that documents the details of the study. Upon understanding, the participant will be asked to give written consent by signing the consent form approved by the ethics committee. Participants may choose to withdraw from the study at any point in time.

Should they choose to do so, their data will be destroyed.

All participants will be given subject identification numbers to which all the data will be tied. The file records that connect each participant to their identification number will be securely kept on lab servers during the duration of the study. After the study is concluded, the file will be destroyed.

This study is carried out using the operating grants of the group of Tohoku University of implementation officer. For the practice of the present research program, no relationship exists between the particular companies. In other words, no conflict of interest exists in this research project.

As previously mentioned, all personal information and data for the experiment are handled by the personal information manager director of Tohoku University. Access to information requires a securely kept key with limited access. These internal checks and balances ensure the security of all data and personal information.

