### Data management

Personal information and data for all experiments are handled by the personal information manager director of Tohoku University. Access to information requires a key that is securely kept and has limited access. These internal checks and balances ensure the security of all data and personal information. After the end of the experimental period, the data will be consolidated, and any information linking data back to the participant will be discarded to ensure that the data is truly anonymous. Data destruction will not be conducted.

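### Destroying the data of randomised participants who withdraw conflicts with the promised intention-to-treat analysis and multiple imputation

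*Protocol article*

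**What the plan says.** All references are to the Protocol article.

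- **Ethics and dissemination:** "Participants may choose to withdraw from the study at any point in time". The consequence follows: "Should they choose to do so, their data will be destroyed". No exception is made for data collected before the withdrawal.
- **Statistical analysis:** "The analysis will be based on the intention-to-treat principle". Later in the section: "All randomized participants are included in the analyses in line with their allocation, irrespective of how many sessions they complete". On incomplete data: "Missing data are imputed using the multiple imputation method", using chained equations in SPSS. The ANCOVA of change scores adjusts for pre-training score, sex and age. The first aim is tested by a Wilcoxon signed-rank comparison of scores before and after surgery in both groups together.
- **Randomization and blinding:** allocation comes after consent and baseline testing.
- **Data management:** after a sentence on consolidating and anonymising the data once the experimental period is over, it says "Data destruction will not be conducted".

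**The concern.** The withdrawal rule and the analysis rule are both stated without qualification, and they cannot both be applied to the same person. Intention to treat needs everyone who was randomised. Multiple imputation needs the observed part of each incomplete record. Deleting the record of a withdrawer removes both.

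Two things are at stake. The report could describe as intention-to-treat an analysis that leaves out some randomised participants. And if withdrawal differs between arms and is related to how patients are doing, the group comparison is biased. Differential withdrawal is plausible. SCRA participants train at home 3–5 times a week, 30 minutes at a time, for 12 weeks, while controls have visits and tests but no training, and the trial is open-label. The section Risks and benefits to participants expects that some may leave early, since it scales the payment to the hours completed.

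**Working it through.** **1. What is lost for one withdrawer.** Randomisation follows baseline testing, so every randomised withdrawer has pre-surgery scores. Anyone leaving during the training weeks would usually also have the scores taken about 1 week after surgery. Deletion removes the pre-training score, sex and age (the ANCOVA covariates) and the earlier scores from which a missing 12-week score would be imputed. Nothing remains to analyse or impute for that person. The complete pre/post-surgery pair also disappears from the Wilcoxon test, although the section Purpose calls the two aims independent.

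**2. How likely the conflict is to arise.** The plan gives no withdrawal rate, so the rate w is assumed. The chance of at least one withdrawal among the planned 50 is 1 − (1 − w)^50:
- w = 2%: 64%
- w = 5%: 92%
- w = 10%: 99.5%

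**3. Size of the bias if withdrawers are deleted.** Let w_S and w_C be the withdrawal proportions under SCRA and control. Let g be the amount, in SD of change, by which leavers do worse than stayers. The stayers' mean exceeds the full-arm mean by w × g, so the unadjusted group difference is shifted by (w_S − w_C) × g. With 25 per arm, the number analysed is 25(1 − w_S) + 25(1 − w_C). The assumed ranges are w_S 10–30%, w_C 5–10% and g 0.3–0.8 SD.

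| Case | w_S | w_C | g | Bias (SD) | Analysed |
|---|---|---|---|---|---|
| Smallest bias | 10% | 10% | any | 0 × g = 0 | 22.5 + 22.5 = 45 |
| Middle | 20% | 5% | 0.5 | 0.15 × 0.5 = 0.075 | 20 + 23.75 = 43.75 |
| Largest bias | 30% | 5% | 0.8 | 0.25 × 0.8 = 0.20 | 17.5 + 23.75 = 41.25 |

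Over the whole range, the number analysed runs from 17.5 + 22.5 = 40 (30% and 10%) to 22.5 + 23.75 = 46.25 (10% and 5%). If all withdrawals come after the 1-week tests, about 4 to 10 complete pairs are lost from the first aim.

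**4. Would keeping the data help?** This was simulated with 25 per arm, no true effect and 4,000 repetitions. Withdrawal occurred in the SCRA arm only, at nominal rates of 10, 20 and 30% (2, 5 and 8 of 25 after rounding), with poorer performers more likely to leave. ANCOVA on stayers was compared with regression imputation from retained scores. A single imputation stood in for multiple imputation, and age and sex were left out. Mean bias, in SD of a score:

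| Withdrawal driven by | Stayers only | Imputed from retained scores |
|---|---|---|
| Pre-surgery score | 0.03, 0.06, 0.09 | about 0.00 throughout |
| Unseen final score | 0.07, 0.15, 0.22 | 0.06, 0.12, 0.19 |

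Retention removes the bias when the scores already collected explain withdrawal. It removes little when withdrawal depends on the outcome that was never seen.

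**The case against.** The strongest reply is that the conflict is narrow. Data are destroyed only when someone withdraws from the study. The intention-to-treat sentence is about how many sessions are completed, and the section Risks and benefits to participants lets people interrupt a test or the training without calling that withdrawal. This stands. A reader might infer that everyone without a final score is lost, or that the planned analysis is impossible from the outset. The documents do not support either: those who stop training or miss a test without withdrawing keep their data and can be imputed, and the conflict bites only from the first withdrawal after randomisation.

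A reader might also take the Data management sentence as a flat contradiction of the withdrawal rule. Its context is the consolidated data after the study, so it is better read as a statement on archiving. It needs a clarification, but the point does not rest on it.

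A third tempting inference is that the bias must favour SCRA because controls have nothing to do. They do attend hospital visits, answer questions on daily habits and take the final tests. Payment rewards staying in the study, and the Discussion concedes that expectations may affect motivation in both groups. The documents do not establish which arm would lose more people, or that leavers do worse.

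Finally, this is a declared pilot. The middle bias of 0.075 SD is about a quarter of the standard error of an unadjusted difference, sqrt(2/25) = 0.28 SD. That lowers the inferential stakes. It does not make the description of the analysis set true.

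**Conclusion.** The point holds for randomised participants who withdraw from the study. For them the deletion rule and the all-randomised, multiply imputed analysis cannot both be carried out, and no other section resolves this. The plan claims a property that its own data rule removes, and an analysis plan written later could not restore destroyed records.

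The contradiction itself needs no assumption. Its size does. The withdrawal rates and the gap are assumed, and the 0–0.20 SD range is for an unadjusted difference, whereas the planned ANCOVA adjusts for pre-training score, sex and age. Zero bias lies within the range. The sign would reverse if controls withdrew more, or if leavers were the better performers.

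**What to change.** 1. In Ethics and dissemination and in the consent wording, separate two events: (a) stopping training or visits, where data already collected are kept and the final tests are still offered; and (b) an express request to delete data. Destroy data only under (b).
2. Report withdrawals and deletions by arm.
3. Recruitment began in January 2016, so some participants may already have consented under the deletion promise. For them, or if the ethics committee requires deletion on every withdrawal, replace the all-randomised and intention-to-treat claims in Statistical analysis with: all randomised participants who did not withdraw their data.
4. Add to Data management that its statement on destruction concerns the consolidated data after the study.

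The cost is an amendment to the consent wording with ethics approval or, failing that, a corrected sentence on the analysis set. No extra patients or scheduled visits are needed. The change will not remove bias when withdrawal depends on the unseen final score, so the counts by arm are needed in any case.

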### Dissemination policy

Results of the study will be formally published in a journal. Participants, healthcare professionals, the public, and other relevant groups will not be individually notified of the results. There are no publication restrictions to note. Authorship of the study belongs to those specifically listed; no professional writers were involved. Currently, no plans exist to grant public access to the full protocol, participant-level dataset, and statistical code.

